#### Exploratory outcomes

This study proposes exploratory indicators and recommends collecting blood for cytokine xii detection, such as IL-1β, IL-2, and TNF-α, and fecal samples for gut microbiota analysis to explore the subsequent mechanisms after obtaining informed consent from participants. All samples will be collected and transported to the central laboratory of Beijing Traditional Chinese Medicine Hospital for unified detection (Figs. 2 and 3).

**Fig. 2 Fig2:**
[figure not shown]
Blood sample collection

**Fig. 3 Fig3:**
[figure not shown]
Stool sample collection

#### Safety assessment

Participants will undergo regular monitoring of blood, urine, feces, liver and kidney function, as well as electrocardiograms on Day 0 and Day 28 of the treatment period. Adverse events will be classified according to the National Cancer Institute’s Common Terminology Criteria for Adverse Events (NCI-CTCAE), version 4.03. Any adverse events, serious adverse events, or adverse drug reactions occurring during the study will be documented with details including severity, relevance to this study, duration, relationship to the trial drug, management measures taken and outcome regression. Follow-up visits will continue until the patient’s condition stabilizes or improves.

### Register, ethical issues, and oversight

Before enrolling participants, we registered the study protocol with the China Clinical Trial Registry (ChiCTR2300072786). The study obtained ethical approval from the Ethics Committee of Beijing Hospital of Traditional Chinese Medicine, Capital Medical University (2023BL02-060-01) and other participating institutions. It is currently being conducted in accordance with the principles outlined in the Declaration of Helsinki regarding risks and benefits, privacy and confidentiality, informed consent, and placebo usage. Supervision will be carried out by Beijing Excellence Future International Pharmaceutical Technology Development Co., Ltd (CRO), with clinical research associates (CRAs) independently monitoring safety, quality, and progress on a quarterly basis.

### Data management

The responsibility for data management lies with Beijing Excellence Future International Pharmaceutical Technology Development Co., Ltd. The Data Manager (DM) of the company has implemented Electronic Data Capture (EDC) based on the Case Report Form (CRF) in ProResearch’s Clinical Research Intelligent Monitoring System, following the previously drafted Data Management and Validation Plan. Clinical Research Coordinators (CRCs) can input data into EDC using their accounts. Any errors or queries identified by the system will be forwarded to CRCs for resolution. Once all data entry issues have been resolved, PI, Sub-Is, and CRCs will lock the database within four weeks. Finally, Beijing Excellence Future International Pharmaceutical Technology Development Co., Ltd exports and transfers the locked database to statisticians for analysis purposes. Only the DM has access to the final trial dataset.

### Statistical analysis

The data will be subjected to two-sided statistical tests using SAS software (version 9.4). Statistical significance was defined as a P value of 0.05 or less. Following data collection, the Full Analysis set (FAS), per-protocol set (PPS), and safety set (SS) will be established. In order to be included in the per-protocol analysis, participants must provide data on the QLQ-LC30 at baseline and at least two additional time points. If a participant meets the withdrawal criteria, their data will not be included in the analysis. Continuous variables will be presented as mean ± SD or as median and IQR. Comparison between groups will be conducted using t-test or Wilcoxon rank sum test for continuous variables, while categorical variables will be expressed as frequency or proportion and compared using χ^2^ or Fisher’s exact test between groups. The survival analysis or Logistic model or Cox regression model will then be constructed for multivariate analysis based on these comparisons. Missing data will undergo multiple imputations to handle them appropriately, allowing for sensitivity analyses by comparing results from complete cases with those from imputed data.

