The withdrawal criteria are as follows: (1) Unexpected rapid progression or radiographic confirmation of progression. (2) Complications or coexisting conditions that prevent continued participation in the trial. (3) Serious adverse events occur that make continuation of the trial inappropriate. (4) Erroneous inclusion in the trial was identified. (5) Safety concerns are identified by the investigators. (6) Participants themselves decide to withdraw. Participants have the right to withdraw from the trial during the course of the trial, meanwhile investigators should attempt to identify and document reasons for withdrawal, such as a perceived lack of treatment effect. Some adverse reactions could not be tolerated, unexplained loss to follow-up, etc.

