#### De-walled Ganoderma Lucidum spore powder

All participants will commence administration on the first day of enrollment and continue for a duration of 2 months. The drugs should be completely dissolved by stirring at a temperature of 100 °C hot water, diluted with cold water or cooled prior to administration two grams twice per day during the initial week, and four grams twice per day from weeks 2 to 8. In parallel, the control group will receive placebo pellets composed of 95% dextrin and 5% de-walled GLSP following an identical protocol. Both TCM granules and placebos are uniformly manufactured by Zhejiang Shouxiangu Pharmaceutical Co., LTD (located at [name]) to ensure similarity in terms of appearance, smell, texture, and taste. Participants are required to return the kit along with its label to the CRC as evidence of timely medication usage for adherence evaluation.

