### Assessments and time-points

Assessments will be conducted biweekly from the beginning of the study until completion (Table 1).

**Table 1 Tab1:** Trial visit schedule

Study stage		Baseline	Therapeutic period				Follow-up period	
Point of visit			1	2	3	4	5	6
Follow-up time points^a^		7 days before treatment	Day 14 of treatment	Day 28 of treatment	Day 42 of treatment	Day 56 of treatment	Day 14 after treatment	Day 28 after treatment
Time point (days)		-7 to 0	14	28	42	56	70	84
Visit windows (days)		± 3	± 3	± 3	± 3	± 3	± 7	± 7
Informed Consent		×						
Inclusion and exclusion criteria		×						
Demographic data		×						
History of diagnosis and treatment		×						
Blood and stool samples collected		×				×		
Laboratory and aided examination	Liver/ Renal/ Blood/ Urine/ Stoolfunction test	×				×		
	Twelve items of cytokines	×				×		
	Imageological examination	×			×			×
	ECG	×				×		
QLQ-C30/ PFS-CV/ EQ-5D		×	×	×	×	×		×
Evaluation of adverse reactions		×	×	×	×	×		×
AE&SAE		×	×	×	×	×		×
Compliance evaluation		×	×	×	×	×		×
Combination drug		×	×	×	×	×		×

*Abbreviations* ECG electrocardiograph, QLQ-C30 Quality of Life Questionnaire for Cancer Patients, PFS-CV Chinese version of the Piper Fatigue Scale, EQ-5D European Five Dimensional Health Scale, AE adverse events, SAE serious adverse event

^a^Patients will be followed up every two weeks

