#### Primary outcome

Fatigue symptoms as adverse reactions to EGFR-TKIs is the primary outcome of this study, which will be evaluated by the EORTC QLQ-C30 Chinese version. The scale will be administered biweekly throughout the treatment period. The outcome endpoint will be determined based on the QLQ-C30 fatigue subscale score on day 56.

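### The stated entry rule for the per-protocol set counts questionnaires and does not require the day-56 fatigue score that is the primary endpoint

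*Protocol article*

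**What the plan says.** The Statistical analysis section of the protocol article names a full analysis set, a per-protocol set and a safety set. It states one positive condition for the per-protocol analysis: "participants must provide data on the QLQ-LC30 at baseline and at least two additional time points". The sentence after it reads "If a participant meets the withdrawal criteria, their data will not be included in the analysis", without saying which set is meant. The same section plans for gaps in the data: "Missing data will undergo multiple imputations to handle them appropriately, allowing for sensitivity analyses by comparing results from complete cases with those from imputed data".

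The Primary outcome section states: "The outcome endpoint will be determined based on the QLQ-C30 fatigue subscale score on day 56". Table 1, under Assessments and time-points, marks the row "QLQ-C30/ PFS-CV/ EQ-5D" at baseline and on days 14, 28, 42, 56 and 84. The visit window at day 56 is ±3 days.

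The section on the study product has participants "return the kit along with its label to the CRC as evidence of timely medication usage for adherence evaluation", and Table 1 marks a compliance evaluation at each treatment visit. The withdrawal criteria, under Settings and participates, cover progression, complications, serious adverse events, wrongful inclusion, safety concerns and the participant's own decision.

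**The concern.** A per-protocol set should hold patients who followed the plan closely enough for the primary comparison to be read in them. At the least, that means patients measured at the primary time point. The stated rule counts forms and treats all post-baseline visits alike, including day 84, which falls 28 days after treatment ends.

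A patient admitted without a day-56 score has nothing observed to contribute to the day-56 comparison. If the analysis uses observed values, the patient is a member of the set but is not analysed. If it uses imputed values, part of the per-protocol result rests on modelled endpoints. The article plans multiple imputation but does not say whether it reaches this set. So neither the number analysed per protocol nor the share of observed endpoints is fixed, and either could be settled after the data are seen.

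**Working it through.** **The plan's own figures.** The article gives no figure for the per-protocol set. Its sample size reproduces. A two-sided two-sample t-test (noncentral t) with difference 15, SD 24.9 and alpha 0.05 gives power 0.9006 at 59 per arm and 0.8956 at 58, so 59 is the smallest size reaching 0.90. With 15% dropout, 59 / 0.85 = 69.4, rounded up to 70 per arm. Nothing below changes this.

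**Which patterns meet the rule.** Inputs: five post-baseline questionnaire visits (days 14, 28, 42, 56, 84, from Table 1), and an entry rule of baseline plus two or more of them.

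- All qualifying patterns: C(5,2) + C(5,3) + C(5,4) + C(5,5) = 10 + 10 + 5 + 1 = 26.
- Qualifying without day 56 (two or more of the other four visits): C(4,2) + C(4,3) + C(4,4) = 6 + 4 + 1 = 11.
- Minimal patterns of exactly two later visits: 10, of which C(4,2) = 6 lack day 56.
- If only the treatment visits count (days 14, 28, 42, 56): 6 + 4 + 1 = 11 qualify, of which C(3,2) + C(3,3) = 3 + 1 = 4 lack day 56. Of the 6 minimal pairs, 3 lack it.

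These count patterns, not patients. The article gives no visit-level missingness, so they show what the rule permits and not how often it will happen.

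**The reverse case.** A patient with baseline and day 56 only has one later form and fails the rule, although the primary endpoint was observed.

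**Does the withdrawal sentence close the gap?** The two sentences can be applied to four kinds of patient, assuming the second governs the per-protocol set:

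- Progresses, or chooses to withdraw, after day 28: passes the form count, removed by the withdrawal sentence.
- Wrongly included: removed by the withdrawal sentence.
- Stays in the trial with forms on days 14 and 28, or on days 42 and 84, but none on day 56: passes the form count and meets no withdrawal criterion, so is kept.
- Stays in the trial and takes little of the product: passes the form count and meets no withdrawal criterion, so is kept unless a condition not shown in the article removes the patient.

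If the withdrawal sentence governs some other set, or all of them, its effect on per-protocol membership cannot be read from the text.

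**The case against.** The strongest reply is that the withdrawal sentence already removes most of the patients at issue. It directly follows the per-protocol condition, so applying it to that set is the natural reading. A patient who stops after day 28 will usually meet one of the listed criteria. This stands. It leaves mainly patients who remain in the trial and miss the day-56 form.

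It also disposes of a figure that a reader might infer. The 15% dropout allowance on 140 patients gives 0.15 × 140 = 21, which could be taken as the number entering without a primary score. That would require every dropout to leave after two later forms and none to be caught by the withdrawal sentence. The allowance is a planning margin and does not forecast who misses day 56.

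A second reply concerns adherence. The rule is worded as a necessary condition in a condensed article, and a cut-off or a list of major deviations may sit in the full protocol or the analysis plan. This also stands. A reader might infer that adherence plays no part in the set, but the article's silence does not show that. It shows only that the published condition is not linked to data collected "as evidence of timely medication usage for adherence evaluation".

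Third, patients without a day-56 score may simply drop out of the t-test, leaving those measured at the endpoint. That is one possible outcome, but the text does not choose it over imputation.

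The name QLQ-LC30 in the rule is a clerical slip. The article otherwise uses QLQ-C30, and no second instrument is implied.

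**Conclusion.** The point holds in a limited form. The one published condition for the per-protocol set does not match the primary endpoint: it admits patients with no day-56 score, and the sentence that follows does not cover a missed form or name the set it governs. This is a stated rule fixed badly. A longer document could add conditions, but this one would still need correcting.

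Its size is 11 of 26 qualifying patterns, or 4 of 11 on treatment visits alone. The number of patients is unknown and is probably small if the withdrawal sentence does apply to this set. The pattern counts rest on Table 1's questionnaire row.

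A reader might conclude that the set cannot serve as a per-protocol check at all. The article does not support that. The set is loosely specified and not aligned with the endpoint, but it is usable once the rule is repaired. Nothing in the article makes it the primary analysis set, and the sample size is unaffected.

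**What to change.** Amend the Statistical analysis section as follows:

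- Replace the count of later forms with a requirement for a baseline QLQ-C30 and an observed day-56 QLQ-C30 fatigue score within Table 1's ±3-day window, that is, days 53 to 59.
- Tie membership to the adherence data already collected, using a threshold fixed before unblinding, or cross-refer to the document that defines it.
- State that the exclusion of patients who meet the withdrawal criteria applies to the per-protocol set only.
- Keep the per-protocol analysis supportive.
- Correct QLQ-LC30 to QLQ-C30 in passing.

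The cost is wording. Every input is already collected and the sample size does not change. The downside is a slightly smaller per-protocol set, offset in part by any patients with baseline and day 56 only, whom the present rule leaves out.

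### The rule excluding participants who meet a withdrawal criterion names no analysis set; read literally, it removes the progression events, part of the safety data and possibly the balance of the fatigue comparison.

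*Protocol article*

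**What the plan says.** The Statistical analysis section of the protocol article announces that "the Full Analysis set (FAS), per-protocol set (PPS), and safety set (SS) will be established". Of these, only the per-protocol set gets an entry rule: "In order to be included in the per-protocol analysis, participants must provide data on the QLQ-LC30 at baseline and at least two additional time points". The next sentence is the one at issue: "If a participant meets the withdrawal criteria, their data will not be included in the analysis". It refers to the analysis in general and names no set. The paragraph ends with a plan for missing values: "Missing data will undergo multiple imputations to handle them appropriately", with complete-case and imputed results compared.

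The withdrawal criteria are listed under Settings and participates. They include:
- "Unexpected rapid progression or radiographic confirmation of progression"
- "Serious adverse events occur that make continuation of the trial inappropriate"
- safety concerns identified by the investigators
- "Participants themselves decide to withdraw", where the reasons to be documented include a perceived lack of effect and intolerable reactions.

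Under Primary outcome: "The outcome endpoint will be determined based on the QLQ-C30 fatigue subscale score on day 56". Under Secondary outcomes, response rate, disease control rate and PFS are assessed by RECIST 1.1, with imaging on days 0, 42 and 84. Under Safety assessment, all adverse and serious adverse events are to be documented.

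**The concern.** Apart from erroneous inclusion, the withdrawal criteria describe things that happen after randomisation and may depend on treatment. Excluding people on that basis means that the groups compared are no longer the groups randomised.

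For the tumour endpoints the problem is structural. Radiographic progression is the event that PFS counts and the failure that disease control counts, and it is also a reason for exclusion. For safety, the participants removed include those whose events were serious enough to end participation. For fatigue, leaving because of progression, toxicity or lack of effect is plausibly linked to the score being compared.

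The rule also undercuts the rest of its paragraph. A full analysis set and a safety set have little purpose if withdrawn participants are taken out of both. Withdrawals are a main source of missing day-56 scores, so removing them leaves little to impute, and comparing complete-case with imputed results could not reveal the resulting bias.

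**Working it through.** **The plan's own figure.** Sample size calculation gives SD 24.9, difference 15, two-sided alpha 0.05 and power 0.90. A two-sample t-test then needs 59 per arm (power 0.9006), and 59 / 0.85 = 69.4, rounded up to 70 per arm or 140 in total. The stated figures reproduce, so sample size is not at issue.

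**Progressions exposed to the rule.** The Introduction quotes a median PFS of 10 to 14 months, for Ex19del with T790M. Assuming exponential PFS with median m months, P(progressed by day d) = 1 − 0.5^(d / 30.4375 / m).
- Day 42 (1.380 months): m = 10 gives 9.1%, or 12.8 of 140; m = 14 gives 6.6%, or 9.2 of 140.
- Day 84 (2.760 months): m = 10 gives 17.4%, or 24.4 of 140; m = 14 gives 12.8%, or 17.9 of 140.

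The only scheduled scan before the day-56 endpoint is at day 42, so about 9 to 13 is the relevant count for the fatigue analysis. The 18 to 24 by day 84 is an upper figure, because day 84 is the last visit and it is unclear whether progression found there counts as withdrawal.

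**PFS and disease control.** With these participants removed, no radiographic progression remains as a PFS event; only deaths without progression could. For disease control at day 42, if progression were the only failure, 13 progressors would give (140 − 13) / 140 = 90.7%. After exclusion it is 127 / 127 = 100%, whatever the treatment does.

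**Response rate.** Take the roughly 80% response rate from the Introduction (112 of 140) and 20 progressors removed:
- none had responded: 112 / 120 = 93%
- half had responded: 102 / 120 = 85%
- 80% had responded: 96 / 120 = 80%

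Inflation is therefore possible but not certain.

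**Fatigue.** Let w be the share withdrawn in an arm and g the points by which withdrawn participants are more fatigued than those retained. The retained mean lies w × g below the arm's full mean. With no true effect and equal g, the spurious difference is (difference in w) × g, in favour of the arm that loses more people. SE = 24.9 × √(1/n₁ + 1/n₂), with 70 randomised per arm. The rates and gaps below are assumptions; the document gives only 15% dropout overall.
- 15% versus 15%, equal gaps: bias 0, type I error 5%.
- 10% versus 20% (63 and 56 retained, SE 4.57): a gap of 15 gives 1.5 points and 6.2%; a gap of 25 gives 2.5 points and 8.5%.
- 5% versus 25% (66.5 and 52.5 retained, SE 4.60), gap 20: 4 points, 4 / 4.60 = 0.87, type I error about 14%. This is a worst case. The 4 points are 27% of the assumed 15-point effect.

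**The case against.** The strongest reply is that the sentence comes straight after the per-protocol entry rule, so that it reads naturally as a second condition for that set. Excluding withdrawn participants from a per-protocol set is ordinary practice. The full analysis set, safety set, imputation, survival models and documentation of every adverse event all suggest that trial-wide deletion was not intended. This stands as a plausible account of the intention, and on that reading the damage is confined to the per-protocol set. It does not remove the point: the preceding sentence names the per-protocol analysis and this one does not, and the article does not say which set is primary. The two readings give different results for primary, secondary and safety outcomes.

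A reader might also infer more than the document supports:
- That all serious adverse events vanish. Only those that make continuation inappropriate trigger withdrawal, and all are still recorded. What is lost, on the literal reading, is withdrawn participants' events at the analysis stage.
- That the response rate must be inflated. The working shows no change if progressors had responded at the overall rate.
- That the fatigue comparison is certainly biased. It is not if withdrawal rates and fatigue gaps are equal across arms.

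Finally, the quoted median PFS is for Ex19del with T790M, whereas the trial admits 19DEL and 21L858R and describes osimertinib as initial treatment. The progression counts indicate scale and are not forecasts.

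The missing definitions of the full analysis and safety sets are no part of this point, since an article may leave them to the full protocol or analysis plan.

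**Conclusion.** The point holds as a badly fixed rule: the exclusion is stated without limit and, followed as printed, conflicts with the analysis sets and imputation beside it. The loss of radiographic progressions from PFS and the drift of disease control towards 100% follow directly from the text. Their scale, about 9 to 13 of 140 by day 42 and up to 18 to 24 by day 84, rests on the quoted median and an exponential curve.

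The effects on response rate and fatigue are risks. Fatigue bias is 1.5 to 2.5 points with a type I error of 6% to 8.5% under the moderate assumptions, 4 points and about 14% in the worst case, and zero with equal rates and gaps. The document does not establish that the sponsor intends to delete these participants from every analysis; it only fails to rule that out. The wording should be corrected before analysis.

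**What to change.** 1. Restrict the exclusion sentence to the per-protocol set, or delete it.
2. Name the full analysis set, comprising all randomised participants, as the primary set for fatigue, PFS, response rate and disease control. Use all QLQ-C30 data collected, and apply multiple imputation to missing day-56 scores, including those of withdrawn participants.
3. Count progression or death as a PFS event. Keep withdrawn participants in the response and disease control denominators with their RECIST best response.
4. Keep everyone who took a dose in the safety set.

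The cost is wording only. The target stays at 140: on the plan's own assumptions, power for 15 points is 0.901 with 59 per arm contributing day-56 data and 0.943 if all 70 per arm do.

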### Sample size calculation

The modeling calculations were conducted using the PASS 15.0 software, employing a Two-Sample t-test Assuming Equal Variance (bilateral test) with the following parameters: alpha = 0.05, power = 0.90, and N1:N2 = 1:1 ratio. The score of fatigue according to QLQ-C30 is the primary outcome measure of our study. In the FLAURA patient-reported outcome using the same scale, a mean fatigue score of 32.2 ± 24.9 was observed in patients with advanced EGFR-mutated NSCLC treated with Osimertinib [14]. Referring to previous literature, it is considered that the minimum clinically important difference (MID) in fatigue subscale is 11.1 and there exists a range of change between 11.1 and 22.2 points within this threshold value range for clinical significance assessment purposes [15]. The use of de-walled GLSP is assumed to result in at least a 15-point increase in fatigue score, indicating potential clinical significance for this drug intervention approach. By calculating N1 = N2 = 59 cases, we determined that the minimum required sample size would be 118 cases. Considering a dropout rate of 15%, adjusting N1 = N2 = 70 cases yields a minimum sample size requirement of 140 cases.

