#### Secondary outcomes

The secondary outcomes are as follows:

The efficacy evaluation of the combination of de-walled GLSP and EGFR-TKIs will be evaluated based on objective response rate (ORR), disease control rate (DCR), and progression-free survival (PFS) according to RECIST 1.1 criteria. Imaging examinations and efficacy assessments will be conducted on day 0, day 42, and day 84 of the treatment period, calculating ORR/DCR, while PFS will be determined by follow-up at each treatment cycle during the follow-up period.

The QoL assessment will be conducted using the QLQ-C30, PFS-CV (Chinese version of the Piper Fatigue Scale), and EQ-5D (European Five Dimensional Health Scale). Participants will independently complete these three questionnaires with assistance from the investigator to evaluate patients’ QoL from a multidimensional perspective. The total score for QLQ-C30 is calculated by summing scores across domains and dividing by the number of items included, which is further linearly transformed using polarization. PFS-CV measures typical fatigue symptoms and is calculated as the mean sum of all topic scores, with subscale scores obtained by averaging four different dimensions separately. EQ-5D quantifies patient health status through five dimensions assessed via a utility index, while a visual scale allows direct scoring by patients on a scale of 0 to 100. QoL will be collected at baseline and each visit.

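### Neither stated rule for patients who leave early gives a sound ORR or DCR: one drops them from the denominator, the other gives them an imputed tumour response

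*Protocol article*

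**What the plan says.** All places are in the protocol article.

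- **Secondary outcomes.** ORR, DCR and PFS follow RECIST 1.1, with this scan schedule: "Imaging examinations and efficacy assessments will be conducted on day 0, day 42, and day 84 of the treatment period, calculating ORR/DCR". Table 1 agrees, with imaging at baseline, day 42 and day 84. The text does not say whether response is read at one scan or as the best over both.
- **Settings and participates, withdrawal criteria.** The first criterion is "Unexpected rapid progression or radiographic confirmation of progression". Others are complications, serious adverse events, safety concerns and the participant's own decision. Intolerable adverse reactions and unexplained loss to follow-up are named among the reasons for withdrawal.
- **Statistical analysis.** A full analysis set, a per-protocol set and a safety set are named. Two rules then bear on patients who leave. The first is that a participant who meets the withdrawal criteria is left out of the analysis. The second is: "Missing data will undergo multiple imputations to handle them appropriately, allowing for sensitivity analyses by comparing results from complete cases with those from imputed data". Neither rule names an outcome, and the section does not say which takes precedence.
- **Sample size calculation.** The trial allows for 15% dropout: "Considering a dropout rate of 15%, adjusting N1 = N2 = 70 cases yields a minimum sample size requirement of 140 cases".

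**The concern.** A patient who leaves before day 42 has no scheduled post-baseline scan, and so no RECIST response unless an unscheduled scan was done. Several of the listed exits are related to outcome. A patient who leaves for rapid progression or intolerance is less likely to be a responder than one who stays and is scanned.

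Under the exclusion rule such a patient leaves the denominator. So does a patient whose progression was seen on a scan, although that outcome is known. Under the imputation rule an unscanned patient receives a response drawn from the experience of scanned patients. The planned check against complete cases cannot reveal the problem, because the complete cases are those same scanned patients.

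ORR and DCR head the list of secondary outcomes and are the direct evidence for the synergy with osimertinib claimed in the title. Rates that are too high would overstate that evidence in each arm. If exits differ between arms, the comparison itself could be distorted.

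**Working it through.** **1. The plan's own figure.** The inputs are "alpha = 0.05, power = 0.90, and N1:N2 = 1:1 ratio", an SD of 24.9 and a 15-point difference in fatigue score. A two-sided two-sample t-test needs 59 per arm (power 0.9006), as stated. For dropout, 59/(1 − 0.15) = 69.4, so 70 per arm and 140 in total, also as stated. The article gives no planning figure for ORR or DCR, so what follows is illustration.

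**2. Inputs for the illustration.**
- Response rate among scanned patients, r = 80% (Introduction, a background figure and not a planning assumption).
- Dropout of 15% (Sample size calculation).
- Exits spread evenly over 84 or 56 days (assumed).
- DCR among scanned patients of 90%, range 85% to 95% (assumed).

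**3. Share m without a day-42 scan.**
- Over 84 days: 15% × 42/84 = 7.5%, or 0.075 × 70 = 5.25 patients per arm.
- Over 56 days: 15% × 42/56 = 11.25%, or 0.1125 × 70 = 7.9 patients per arm.

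**4. Imputation route.** Imputation under missing at random returns about r. Counting unscanned patients as failures returns r(1 − m). The gap is r × m.

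| | m = 7.5% | m = 11.25% |
|---|---|---|
| ORR, imputed | 80% | 80% |
| ORR, unscanned = non-response | 0.80 × 0.925 = 74% | 0.80 × 0.8875 = 71% |
| Gap | 6 points | 9 points |
| DCR gap at r = 90% | 6.75 points | 10.1 points |

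For DCR between 85% and 95%, the gap runs from 0.85 × 0.075 = 6.4 points to 0.95 × 0.1125 = 10.7 points. A small multiple-imputation simulation at 70 per arm, with m of 5%, 10% and 15%, confirmed that the imputed ORR stays at about 80% whatever the leavers' true response.

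**5. Dependence on the leavers' true response, q.** Measured against the rate that would have been seen with everyone scanned, the excess is m(r − q).
- q = 0: 6 to 9 points.
- q = 40%: 0.075 × 0.40 = 3 points to 0.1125 × 0.40 = 4.5 points.
- q = 80%: 0.

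**6. Exclusion route.** Suppose 56 of 70 patients respond (80.0%) and the early progressors are removed.
- 4 removed: ORR 56/66 = 84.8%. If they are the only progressors, DCR rises from 66/70 = 94.3% to 100%.
- 8 removed: ORR 56/62 = 90.3%. DCR rises from 62/70 = 88.6% to 100%.

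For scale, the Introduction cites a median PFS of 10 to 14 months. Under an exponential curve, 1 − exp(−ln 2 × (42/30.44)/median) gives 9.1% and 6.6% progressing by day 42, which is about 6 and 5 of 70. These counts bear on the exclusion rule only. Progression seen on a scan is a known outcome, not a missing one.

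**7. Between arms.** With equal exits and equal rates the difference is zero whether leavers are imputed or counted as failures. With 5% against 15% unscanned (assumed) and r = 80% in both arms, counting leavers as failures gives 76% against 68%, an 8-point difference. Imputation gives none.

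**The case against.** **The imputation sentence names no outcome, and details belong in the analysis plan.** It may be meant for the questionnaires, and the imputation model and the scoring of non-evaluable patients are often left to a plan that is not shown. This stands in part: silence on a non-responder rule would not be a finding by itself. But the article does more than stay silent. It publishes two general rules without limits, and neither treats an unscanned leaver as a failure.

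**The exclusion sentence may define only the per-protocol set.** It follows directly on the per-protocol condition, so that reading is possible. On that reading, early leavers in the full analysis set fall to the imputation rule, and the point remains by the other route.

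**Imputation as the only stated rule.** A reader who looks at the imputation sentence alone might infer this. The documents do not support it: the same paragraph excludes withdrawn participants, and the withdrawal criteria cover most early leavers. Read literally, those patients are dropped and not imputed.

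**A larger inflation.** A reader might take the whole 15% dropout as unscanned and reach 12 points for ORR (0.80 × 0.15) and about 13.5 for DCR (0.90 × 0.15). Under best overall response, a patient who leaves between day 42 and day 84 already has a scan, so on the assumed timings only 7.5% to 11.25% are unscanned. Even that share is generous, since some early leavers will have had a scan that confirmed progression.

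**Inflation is conditional.** This stands. Imputation overstates the rates only if leavers respond less often than completers, or if the target counts them as failures. A model using arm and reason for exit could reduce the excess; the article specifies none. The exclusion could also remove some patients who had responded before leaving.

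**Conclusion.** The point holds as a badly fixed rule for two secondary endpoints. The exclusion removes early leavers and documented progressors from the denominator. Unrestricted imputation, checked only against complete cases, gives unscanned patients about the response of scanned ones. Because the listed exits include rapid progression, serious adverse events and intolerance, both routes tend to put ORR and DCR too high.

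On the imputation route the size is up to 6 to 9 points for ORR and, at an assumed 90%, about 7 to 10 points for DCR. This rests on the 80% background rate, the 15% dropout, even exit timing and no response among leavers. It is smaller if some leavers would have responded. On the exclusion route, removing 4 early progressors moves ORR from 80.0% to 84.8%.

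A reader might infer that the comparison between arms is necessarily biased. The documents do not support that: with equal exits and rates the difference is unaffected, and no arm-specific exit rates are given. The risk is that a difference is masked or created if exits differ by arm. The primary outcome, day-56 fatigue, is not touched by this point. The change should be made, but the trial's main conclusion does not depend on it.

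**What to change.** In Secondary outcomes and Statistical analysis:

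1. Analyse ORR and DCR in all randomised patients (FAS), as best overall response over the day-42 and day-84 scans.
2. State that the exclusion of withdrawn participants does not apply to these endpoints.
3. Count a patient with no evaluable post-baseline scan as a non-responder and as not disease-controlled.
4. Keep documented progression as progression.
5. Limit multiple imputation to the questionnaire scores.
6. Show the rates among evaluable patients as the sensitivity analysis.

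The cost is a few sentences of analysis wording, with no new scans, data or patients. The downside is that reported rates will be somewhat lower and some unscanned true responders will count as failures. The evaluable-patient analysis shows how much that matters.
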